### Statistical analysis

Summary scores of outcomes will be stratified by participation in the intervention versus control groups and compared using chi-square tests, for binary or categorical outcomes, and t-tests and analysis of variance (ANOVA) for continuous outcomes. The equivalence of the two study groups at baseline will be compared across a range of background variables. Study hypotheses will be tested using an “intent to treat” model. Participants who drop-out during the study and don’t provide at least 3-month follow-up data will be removed from the analysis. Outcomes will be evaluated using generalized linear mixed models (GLMM), commonly used in longitudinal data analysis for both binary and continuous outcomes. If EMPWR is effective in increasing condom use at last sex, mediation analysis will be conducted to identify whether changes in substance use and mental health symptoms are responsible for this change.

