### Randomization and sample size

This study will use a randomized controlled group design; the unit of randomization will be the individual. Unique participant identification numbers will be used to randomize individuals to one of two study groups: intervention or control. A 1:1 allocation ratio and stratified randomization technique will be used to ensure a 1:1 allocation of study conditions across males and females and age group (i.e., 18–29 and 30–49). Study group allocation will be revealed to participants after completing the baseline assessment.

Sample size and statistical power estimates are predicated on the primary hypothesis that our intervention will increase self-reported condom use in the intervention group compared to the control group. A sample size of 240 (120 per study group) will provide >80 % power to detect a 20 % difference in condom use at last sex where alpha = 0.05. The effect size is based on observed impacts in past trials of the original EBI (Project RESPECT) [33, 40]. The study team will over-recruit to allow for participant withdrawal and drop-out between the baseline and 6-month follow-up. Based on retention rates from past randomized controlled trials conducted by the study team with the target population, it is estimated that 300 participants will need to be recruited to retain a final sample size of *n* = 240 [34, 41, 42].

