### Outcomes

#### Primary outcome

The primary outcome for this trial will be condom use at last sex.

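### Crude between-arm tests and a GLMM are both named for the same outcomes without a ranking, and the crude tests ignore the stratification factors and baseline condom use

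*Protocol article*

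**What the plan says.** The Statistical analysis section gives two between-arm analyses. Summary scores of the outcomes, split by study group, are to be "compared using chi-square tests, for binary or categorical outcomes, and t-tests and analysis of variance (ANOVA) for continuous outcomes". Later in the same paragraph: "Outcomes will be evaluated using generalized linear mixed models (GLMM), commonly used in longitudinal data analysis for both binary and continuous outcomes". Between the two stand a sentence on baseline equivalence and a statement that hypotheses are tested by intention to treat. Neither analysis is called primary or descriptive, and no covariate is named for either.

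Three other parts of the article bear on this:

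- **Randomization and sample size.** A "stratified randomization technique will be used to ensure a 1:1 allocation of study conditions across males and females and age group", with age split at 18–29 and 30–49.
- **Data collection.** Measures are taken at baseline, 3 months and 6 months, and condom use at last sex is among them.
- **Overview and hypotheses.** The between-arm hypothesis is placed at 3 months; the 6-month measurement is there to see whether any increase lasts.

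On the outcome, the article says: "The primary outcome for this trial will be condom use at last sex". On size: "A sample size of 240 (120 per study group) will provide >80 % power to detect a 20 % difference".

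**The concern.** Two questions follow.

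1. **Which result counts?** If a chi-square test and a GLMM contrast disagree, the article gives no rule for choosing. Whoever reports the trial could pick the smaller p-value, and the error rate of the whole procedure then exceeds that of either test.
2. **Is design information used?** Stratified allocation balances the arms on sex and age group. A test that ignores those factors tends to have a standard error too wide for the design. Baseline condom use is likely to predict later condom use, and a chi-square test makes no use of it. If the crude tests decide, power already paid for goes unused.

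**Working it through.** **Inputs from the article.** 120 per arm analysed; "20 % difference in condom use at last sex where alpha = 0.05"; 1:1 allocation stratified by sex and age group; 300 recruited to keep 240.

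**Assumptions.** Two-sided alpha. The 20 % is read as percentage points; read as a relative difference, power would be only 11–73 % for control rates of 20–70 %, so the percentage-point reading is the one that fits. The control rate is not given, so 10–70 % was run. The correlation ρ between baseline and follow-up condom use is not given, so a range is shown.

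**1. The plan's own figure.** With p̄ the mean of the two rates,

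power = Φ{ [ |p₂−p₁|√n − 1.96√(2p̄(1−p̄)) ] / √(p₁(1−p₁)+p₂(1−p₂)) }

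For 40 % v 60 % and n = 120: (0.2 × 10.954 − 1.96 × 0.7071) / 0.6928 = 1.162, and Φ(1.162) = 87.7 %. This is the least favourable pair of rates; 30 % v 50 % gives 89.0 % and 20 % v 40 % gives 92.7 %. The largest requirement for 80 % power is 97 per arm, or 107 with continuity correction. Recruitment also reproduces: 240/(1 − 0.20) = 300.

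**2. Gain from baseline adjustment.** As an approximation, adjusting for a covariate with correlation ρ divides the variance by 1/(1 − ρ²), so the effective n per arm is 120/(1 − ρ²). The equivalent number of participants is 240ρ².

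| ρ (assumed) | Effective n per arm | Power, 40 % v 60 % | Power, 40 % v 55 % | Equivalent participants |
|---|---|---|---|---|
| 0 | 120 | 87.7 % | 64.5 % | 0 |
| 0.1 | 121.2 | 88.1 % | 64.9 % | 2 |
| 0.2 | 125.0 | 89.0 % | 66.3 % | 10 |
| 0.3 | 131.9 | 90.6 % | 68.6 % | 22 |
| 0.4 | 142.9 | 92.6 % | 72.1 % | 38 |
| 0.5 | 160.0 | 95.1 % | 76.9 % | 60 |

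The 15-point column shows sensitivity only; the plan is sized on 20 points.

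**3. Simulation check.** 3,000 trials per setting, 240 participants, arms balanced within sex-by-age strata, control rate 40 %. A two-proportion z-test (equivalent to chi-square) was set against a single-time-point logistic model with sex, age group and baseline condom use. For 20 points and observed baseline correlations of 0.12–0.49, the crude test had 86–87 % power and the adjusted model 88–95 %. This agrees with step 2.

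**4. Type I error with two unranked tests.** In the same simulation under no effect (Monte Carlo SE about 0.4 points):

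| Rule | Type I error |
|---|---|
| Crude test alone | 3.3–5.1 % |
| Adjusted model alone | 4.5–5.4 % |
| Either may be claimed | 5.3–7.3 % |

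The inflation is small because the two tests use the same 3-month data. A GLMM may give a different contrast. With 4,000 null trials per setting (assumed strata log-odds ratio 0.5, random-intercept SD 1–2), claiming either the 3-month chi-square or an adjusted contrast pooled over 3 and 6 months gave 8.2–8.4 %. Claiming either the chi-square or a change-from-baseline contrast gave 8.3–9.2 %. These used a cluster-robust logistic model and a difference in change as stand-ins, because the article does not specify the GLMM.

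**The case against.** The best defence is that the paragraph can be read as a sequence: simple tables with tests first, then the GLMM as the real analysis. On that reading the crude tests decide nothing. The article is also silent about GLMM covariates, not opposed to them, and such a list is commonly left to a full protocol or analysis plan that is not shown. A GLMM that includes the baseline visit would already use some of the baseline information.

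Much of this stands, and it rules out several stronger readings:

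- **That the plan loses precision.** It does so only if the crude tests decide, or if the GLMM omits these terms. The article establishes neither.
- **That the trial is underpowered without adjustment.** It is not; the stated power reproduces on the crude test.
- **That every outcome could be baseline-adjusted.** Starting self-administered STI sampling and following up STI treatment arise from the trial's own test offer, so they have no natural baseline value.
- **That a GLMM odds ratio cannot be set against the planned 20 points.** In a random-intercept logistic model, a marginal odds ratio of 2.25 (40 % v 60 %) becomes exp(ln 2.25 × √(1 + 0.346 SD²)), that is 2.56 at SD 1 and 3.50 at SD 2. But the article fixes neither link nor random-effect structure, the SD is assumed, and model results can be standardised to a risk difference.

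The defence does not remove the missing ranking. Baseline equivalence has its own sentence, so the chi-square sentence is about outcomes. The intention-to-treat statement names a population and no test. The sequential reading is reasonable, but nothing in the text commits the trial to it.

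**Conclusion.** The point holds in a limited form. The article names two between-arm analyses of the same outcomes and does not say which decides. The crude ones, as written, leave out the stratification factors and baseline condom use.

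- **Power.** At the planned difference with the least favourable rates (40 % v 60 %), adjustment would move power from about 88 % to 89–95 % for ρ of 0.2–0.5. At ρ = 0.1 the gain is under half a point. ρ is assumed throughout.
- **Type I error.** Modestly above 5 % if either test may be claimed: about 5–7 % when both target the 3-month comparison, possibly 8–9 % if the GLMM contrast is a different one. Both ranges come from stand-in models under assumed settings.

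A reader might infer that the sample size is inadequate or that the primary result would be invalid. Neither follows: planned power exceeds 80 % unadjusted, and each test alone runs at or below about 5 %. The change is worth making because it settles which result counts and costs little.

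**What to change.** Name one decisive analysis in the Statistical analysis section:

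- **Model.** A GLMM on the 3- and 6-month outcomes with arm, visit, arm-by-visit, sex stratum and age stratum as fixed effects and a participant random intercept.
- **Baseline value.** Add it for outcomes that have one (condom use, number of partners, substance use, symptoms). Leave it out for STI sample initiation and treatment follow-up.
- **Primary contrast.** The arm difference at 3 months, in line with the hypothesis in Overview and hypotheses.
- **Reporting.** Give the model estimate and also a standardised (marginal) risk difference with 95 % CI, which is the scale on which the trial is sized.
- **Crude tests.** Label the chi-square, t-test and ANOVA comparisons descriptive.

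The cost is a few sentences and some code; the variables are already collected, and neither sample size nor visits change. The small downside is that adjustment in a logistic-type model makes conditional and marginal effects differ, so the plan must say which one each reported figure is.

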## Methods/Design

### Overview and hypotheses

A two-arm randomized controlled trial (RCT) will be used to test the efficacy of the EMPWR intervention to increase high-risk adult’s condom use at last sex compared to a control group (see Fig. 1). The intervention consists of two sessions which aim to enhance participant’s sense of self-risk, identify practical risk-reduction steps, and reinforce positive behavior change through a risk-reduction plan. The study team hypothesizes that there will be an increase in condom use following delivery of the two sessions. At 3 months follow-up, the study team hypothesizes that there will be a higher rate of condom use during sex amongst participants in the intervention group compared with the control group. At 6 months follow-up, condom use will again be measured to see if any increases were maintained over time. The study team hypothesizes any effects of the intervention on condom use behavior will be mediated by participant’s substance use and mental health status.

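### The analysis is labelled intent-to-treat but removes randomised drop-outs without 3-month data, so the planned set is a modified intent-to-treat set, and the status of 6-month-only participants is unclear

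*Protocol article*

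**What the plan says.** Two consecutive sentences in the protocol article, Statistical analysis, define who is analysed. The first: "Study hypotheses will be tested using an “intent to treat” model". The second says that participants who drop out and do not "provide at least 3-month follow-up data will be removed from the analysis". The same paragraph names generalised linear mixed models (GLMM) as the method for evaluating outcomes.

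Other sections bear on the rule:

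- **Primary outcome:** "The primary outcome for this trial will be condom use at last sex".
- **Overview and hypotheses** places the between-group comparison at the first follow-up: "At 3 months follow-up, the study team hypothesizes that there will be a higher rate of condom use during sex". The 6-month measurement is there to see whether any gain lasts.
- **Randomization and sample size** counts losses over the whole follow-up: "The study team will over-recruit to allow for participant withdrawal and drop-out between the baseline and 6-month follow-up". It plans 300 recruited to keep 240, and says that participants learn their arm once baseline is done.

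**The concern.** An intent-to-treat analysis takes everyone randomised, in the arm assigned. The second sentence takes people out because of something that happens after randomisation. It acts on the time point where the main hypothesis sits, so it shapes the primary result.

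Loss unrelated to arm and outcome cannot be taken for granted here. Participants know their arm. The intervention arm has two counselling sessions that the control arm does not. Everyone is recruited after a recent binge episode, suicidal ideation or both. If people leave at different rates in the two arms, or if those who leave differ in condom use between arms, the remaining groups are no longer the groups that were randomised.

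A second problem is the meaning of the rule. A participant absent at month 3 and present at month 6 counts as retained in the sample-size section, and the GLMM can use that record. The removal sentence can be read as keeping or as deleting that person. Two analysts could build different datasets from the same text.

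**Working it through.** **1. The plan's own figures.** With 120 per group, a 20-point absolute difference and two-sided alpha 0.05 (sidedness and the control rate are not given, so both are assumed), power is lowest at 40% against 60%, where it is 87.7%. It is 97.6% at 10% against 30%. The claim of more than 80% holds. Recruitment: 240 / (1 - 0.20) = 300, so the plan allows for 60 losses, or 20%. The sample size is not in error.

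**2. How many the rule removes.** The 60 are losses by 6 months. The rule concerns drop-outs without 3-month data. The article does not give that number, so 60 is an upper bound.

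**3. What the rule can do to the comparison.** The article gives no loss by arm and no condom use among those lost, so these inputs are assumptions: 150 randomised per arm and a true rate of 40% in both arms (no effect). Let m be the fraction removed in an arm and q the condom-use rate among those removed. The rate among those kept is

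(0.40 - m × q) / (1 - m).

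With 25% removed from intervention, 15% from control and q = 20%:

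- Intervention: (0.40 - 0.25 × 0.20) / 0.75 = 0.35 / 0.75 = 46.7%, n = 112.5
- Control: (0.40 - 0.15 × 0.20) / 0.85 = 0.37 / 0.85 = 43.5%, n = 127.5
- Spurious difference d = +3.1 points

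A two-proportion test stands in for the GLMM at one time point. The pooled rate is 0.45, giving a null standard error se0 = √(0.45 × 0.55 × (1/112.5 + 1/127.5)) = 0.0644. The unpooled standard error se1 is 0.0643. The probability of rejection is

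1 - Φ((1.96 × se0 - d) / se1) + Φ((-1.96 × se0 - d) / se1) = 7.8%, against a nominal 5%.

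The same method gives this range:

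| Removed, intervention / control | Condom use among removed, intervention / control | Bias (points) | Rejection |
|---|---|---|---|
| 20% / 20% | 20% / 20% | 0 | 5.0% |
| 25% / 15% | 20% / 20% | +3.1 | 7.8% |
| 15% / 25% | 20% / 20% | -3.1 | 7.8% |
| 20% / 20% | 20% / 40% | +5.0 | 12.2% |
| 20% / 20% | 40% / 20% | -5.0 | 12.2% |
| 30% / 10% | 20% / 20% | +6.3 | 16.5% |

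Every row removes 20% overall, the upper bound from step 2. If only half as many were removed (12.5% and 7.5%, q = 20%), the bias would be 0.375 / 0.875 - 0.385 / 0.925 = 42.9% - 41.6% = +1.2 points.

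**4. The 6-month-only case.** The removal sentence sets two conditions: dropping out, and not providing at least 3-month data. Someone who returns at month 6 arguably has not dropped out, and so stays. But if 3-month data are read as the minimum for inclusion, that person goes. The sample-size section counts retention at 6 months and so keeps them. The text does not settle which reading is meant.

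**The case against.** The best defence is that this is a common modified intent-to-treat set, disclosed in the sentence straight after the label. Participants with no follow-up also add little direct information on the treatment effect in a GLMM, so removing them changes the model estimate little. That second point stands. Deleting the rule does not by itself remove bias from people who are never seen again. The disclosure does not rescue the label, because a reader of the results would take intent-to-treat to mean everyone randomised.

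Imputation models and sensitivity analyses are usually left to the statistical analysis plan, which is not shown, so their absence from the article is no finding. The finding is the stated removal rule, which contradicts the stated principle.

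A reader might infer more than the article supports:

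- **That everyone without 3-month data is deleted.** The rule also requires drop-out, so deletion of 6-month-only participants is a possible reading and not a certainty.
- **That this is a full completer analysis.** People with 3-month but no 6-month data stay in.
- **That the effect will be overstated, for example 20 points reported when the all-randomised effect is 16.** That example takes 60% against 40% among those observed and 20% lost per arm, with all the lost at 40%: 0.8 × 60% + 0.2 × 40% - 40% = 16 points. It assumes that intervention drop-outs gain nothing. Neither a GLMM nor imputation by arm would recover the 16 unless baseline variables explained the gap; a shift (delta) analysis could address it. The direction is an assumption too.
- **That extreme-case bounds count against this rule.** For an observed 20-point effect with 20% missing per arm they are 0.8 × 20 - 20 = -4 and 0.8 × 20 + 20 = +36 points. They follow from the missing data under any analysis rule.

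**Conclusion.** The contradiction is real and lies in the text as written. The analysed set is a modified intent-to-treat (3-month-completer) set, selected after randomisation and after the arm is known, and it cannot be reported as intent-to-treat. The handling of 6-month-only participants is ambiguous and fits poorly with retention being counted at 6 months.

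The effect on the result cannot be fixed from the article. It is zero when loss and outcomes among the lost are alike in both arms. In the central scenario it is about 3 points in either direction, with about 8% rejection under no true effect. That scenario rests on assumed rates and on the full 20% being removed, which is an upper bound. The article does not support a statement that the plan overstates the effect, only that it could be biased in either direction.

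**What to change.** 1. Delete the removal sentence. State that all randomised participants are analysed in their assigned arm, with the GLMM fitted to every available 3- and 6-month observation. Say explicitly that participants with only a 6-month visit are included.
2. Add a sensitivity analysis over all randomised participants, because the GLMM alone does not correct for people with no follow-up. One option is multiple imputation from arm, the randomisation strata and baseline condom use, substance use and symptoms, followed by a delta (tipping-point) shift that shows how different the lost would have to be to change the conclusion. The detail can sit in the statistical analysis plan.
3. Keep the 3-month set only as a sensitivity analysis, labelled modified intent-to-treat.

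The cost is wording and modest programming, with no new data. The estimate may turn out less favourable.

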## Discussion

This study protocol presents one of the first randomized controlled trials to assess the efficacy of an adapted evidence-based intervention for reducing sexual risk behaviors among AI adults with substance use and mental health problems. A limitation of the study is that sexual behavior, substance use and mental health are measured by self-report. While self-report is the most widely used methodology to assess behavior change, it is not without biases. This study utilizes a computerized assessment administration (ACASI) which has shown to mitigate these potential biases [45]. Also, we can triangulate self-reported outcomes with STI incidence biomarkers. Another limitation is a short follow-up period; while typical of behavior change research we may have less capability to demonstrate long-term intervention efficacy. Next, the surveillance system from which we will recruit is unique to the participating community and may not be replicable in other contexts. Also some individuals may not associate their mental health or substance use problems with sexual risk-taking and may be less inclined to enroll in the study. Study staff are trained to discuss the relationship between substance use, mental health and sexual risk taking when a person is approached for participation.

There are many strengths of this study including the use of an evidence-based intervention adapted to fit the context of the participating community while keeping the core components intact. If EMPWR proves feasible, acceptable and efficacious, the process utilized to adapt Project RESPECT may be translated to other communities or other EBIs. Another strength of the study is that it aims to engage a high-risk population who may not be captured in the IHS system. Further, the client-centered approach allows tailoring to an individual’s readiness for behavior change. Including self-administered sample collection for STI screening, proven feasible and acceptable in the participating community, further breaks down healthcare access barriers. Finally, the design of EMPWR allows for easy uptake and dissemination by health systems through community health worker programs. This includes IHS’s Community Health Representative and Public Health Nursing departments.

To our knowledge, this is the first randomized controlled trial of a brief risk-reduction intervention paired with self-administered STI screening in an AI community. If EMPWR proves efficacious, there will be a program for AI adults with mental health and substance use problems to reduce their high-risk behaviors. Additionally, we may deepen our understanding of the relationship between sexual behavior, substance use, and mental health risk which may be beneficial to other AI communities and high-risk populations.
